### Glucose variability evaluation

CGMS will be utilized for this evaluation. Subjects will be admitted to the laboratory in the morning at approximately 08.00 hours, 24 hours before the exercise session, when the glucose sensor (Sof-SensorTM; Medtronic Mini-Med Inc., Northridge, CA, USA) will be inserted subcutaneously. The sensor is a glucose oxidase-based platinum electrode that is inserted through a needle into the subcutaneous tissue of the anterior abdominal wall, using a spring-loaded device (Senserter, Medtronic Mini-Med Inc.).

Glucose oxidase catalyzes the oxidation of glucose in the interstitial fluid, which generates an electrical current. The current is carried by a cable to a pager-sized monitor that analyzes the data every 10 seconds and reports average values every 5 minutes, to give a total of 288 readings per day. Glucose profiles will be collected on the day before (day 1), the day of (day 2), and the day after (day 3) the submaximal exercise test. Sensor readings will be calibrated with a glucose monitor (Accu-Check Performa; Roche Diagnostics) using four finger-stick blood samples for each 24 hours. Each sensor will be used continuously for up to 48 hours. All patients will have been instructed previously about the operation of the monitor, which includes event registration for meals, and inserting capillary glucose values for calibration.

Glucose variability will be assessed from a series of absolute values of glucose, obtained by the CGMS, sampled every 5 minutes. Each method will be used as reported in the literature and according to its limitations. Glucose variability will be evaluated using conventional analysis and other mathematical methods generally applied to biological series, here called “non-conventional analysis of glucose variability.” Conventional analysis of glucose variability will be constructed from the statistical properties of the series, to obtain the following indices: MAGE [6], glucose variance (VAR), glucose coefficient of variation (CV%), and glucose SD, all normalized by the mean blood glucose in each period [15, 16]. These indices, except MAGE, will be calculated for every 6 hour block of glucose values to obtain the measures according to the specific period of the day. The MAGE index will be calculated for the whole signal (24 hours), and its calculation is based on the differences between consecutive points, considering those which are higher than 1SD [16].

Non-conventional analysis of glucose variability will be conducted using two methods applied to the glucose series: a linear method based on spectral analysis, and an integrated non-linear approach to the complexity analysis, called symbolic analysis. Spectral analysis is a linear method that allows quantification of the oscillatory components from time series by autoregressive models widely applied for heart rate and arterial pressure series [17]. Symbolic dynamics relies on the calculation of Shannon entropy of the distribution of patterns lasting three measures and the classification of frequent deterministic patterns lasting three measures, and distributes deterministic patterns of the group into four categories according to the number and pattern: 1) no variation (0 V), 2) one variation (1 V), 3) two like variations (2 LV), and 4) two unlike variations (2 UV) [18]. This method has been fully described and validated previously to glucose curves [7].

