## Background

Cardiovascular disease is the main cause of mortality among people with type 2 diabetes mellitus (T2DM) [1, 2]. Accelerated atherosclerosis in these patients is preceded by endothelial dysfunction, inflammatory burden, and increased lipid peroxidation, all leading to enhanced macrophage foam cell formation [2]. In addition to the average blood glucose concentration, acute glycemic fluctuations from peaks to nadirs (glucose variability) may be involved in the development of diabetic complications [3], as they contribute to the generation of excessive protein glycation and oxidative stress [4]. High glucose variability has been shown to be associated with endothelial dysfunction in patients with T2DM and optimal metabolic control [5]. Currently, the mean amplitude of glycemic excursion (MAGE) is one of the most used methods for detecting significant swings in glycemia [6], but other tools may be useful to identify disturbances in glucose variability [7].

Some current treatments for T2DM have already been tested concerning their possible effects in reducing glucose variability as well as reducing glycated hemoglobin (HbA1c) [8]. Exercise, which is one of the cornerstones of treatment for hyperglycemia in T2DM because of its beneficial effect on HbA1c [9], was recently shown to reduce glucose variability in addition to its acute effects on reducing glucose levels [7]. Vildagliptin and sitagliptin are two drugs that were recently evaluated in a study focusing on possible differences in daily glucose fluctuations in patients with T2DM inadequately controlled with metformin, and it showed that vildagliptin was more effective in flattening acute glucose fluctuations over a day [8]. Moreover, acarbose was superior to glibenclamide in reducing MAGE. Therefore, aside from their absolute glucose-lowering effect, it is evident that other effects of different anti-diabetic agents might also be different [10].

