### Outcomes

The primary outcome will be glucose variability evaluation, as evaluated by conventional and non-conventional methods. Secondary outcomes will include oxidative stress, endothelial function, and metabolic and cardiovascular responses to exercise. Table 1 shows the measures that will be evaluate to reach the outcomes.

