### Sample size calculation

According to data reported by Marfella *et al*. [8], a total sample size of 20 patients (allowing for a dropout rate of 10%) should allow detection of a difference between groups with MAGE levels (mean ± SD) of 25.0 ± 16 mg/dl at week 12, assuming statistical power of 90%, and a significance level of 1% (two-sided, two-sample *t*-test).

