Based on the results of the 24 hour ABPM, the mean 24 hour systolic BP (SBP) and diastolic BP (DBP) will be calculated for each patient, before and after treatment. Three different parameters of SBP variability will be calculated: 1) time–rate index (rate of change in SBP over time in mm Hg/min, defined as the first derivative values of SBP by time); 2) coefficient of variation of the 24 hour SBP (SD/mean pressure × 100%); and 3) mean of the SD of the 24 hour SBP. The time–rate index allows the calculation of the sum of angular coefficients, and aims to measure how fast or how slow SBP values are and in which direction they change. The measure will be calculated using the formula,

where *r* is the rate of BP variability over time (considering the differences between BP measurements at each time interval) and *N* is the number of recordings [24]:

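### Dividing every conventional glucose-variability index by mean glucose normalises CV% twice and takes MAGE off the mg/dl scale on which the trial was sized

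*Protocol article*

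**What the plan says.** The Outcomes section makes these indices part of the primary outcome: "The primary outcome will be glucose variability evaluation, as evaluated by conventional and non-conventional methods". The only definitions of the conventional ones are under Glucose variability evaluation. That section names MAGE, variance (VAR), "glucose coefficient of variation (CV%), and glucose SD, all normalized by the mean blood glucose in each period". All except MAGE are computed in 6-hour blocks. MAGE is computed on the whole 24-hour signal, and "its calculation is based on the differences between consecutive points, considering those which are higher than 1SD". The signal is described just before: "Glucose variability will be assessed from a series of absolute values of glucose, obtained by the CGMS, sampled every 5 minutes". The same paragraph adds a general assurance: "Each method will be used as reported in the literature and according to its limitations".

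Three other places bear on this:

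- Sample size calculation sizes the trial on "MAGE levels (mean ± SD) of 25.0 ± 16 mg/dl at week 12".
- Background describes variability as "acute glycemic fluctuations from peaks to nadirs (glucose variability", closing the bracket there.
- Cardiovascular evaluation, for blood pressure, spells out a "coefficient of variation of the 24 hour SBP (SD/mean pressure × 100" per cent, so the authors' own CV is already divided by the mean once.

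**The concern.** A coefficient of variation is by definition relative to the mean. A rule that divides all four indices by the mean therefore either divides CV% twice or makes the normalised SD a copy of it. It also changes the scale of MAGE, the one index with a power calculation.

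This matters because mean glucose is likely to move in this trial. Patients enter with HbA1c of 7.5% to 10% and receive an added glucose-lowering drug, and the plan compares before with after by paired t-test. One arm has its dose adjusted towards a glucose target and the other does not, so the arms may also differ in mean glucose. The Background notes that exercise acutely lowers glucose, so 6-hour blocks after the test may have lower means than blocks before it. In each comparison, a doubly normalised CV% would show a change in variability that is only a change in the mean.

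For MAGE, the article does not settle whether mg/dl or a ratio to the mean is analysed. The choice could then be made after the data are seen.

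**Working it through.** **Inputs.** From the article: the four indices and the rule dividing them by the mean; 5-minute sampling, 288 values a day; MAGE 25.0 and SD 16 mg/dl; two-sided 1%, 90% power, 10% dropout, total 20. The article gives no mean glucose, no within-day SD and no SD for MAGE/mean. All such values below are assumptions for illustration.

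**The plan's own figure.** Normal approximation, 1:1 allocation assumed: n per arm = 2 × (2.576 + 1.282)² × (16/25)² = 2 × 14.88 × 0.4096 = 12.2, so 13 per arm, 26 in total, and 26/0.9 = 29 with dropout. The exact t calculation gives 14 per arm, 28, and 32 with dropout. The stated 20 is not reproduced at 1%. At two-sided 5% the normal approximation gives 9 per arm, and 18/0.9 = 20. That is a separate matter. What counts here is that the inputs are in mg/dl.

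**CV% divided by the mean.** CV%/mean = 100·SD/mean².

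| Assumed profile | SD/mean | CV% | CV%/mean |
|---|---|---|---|
| SD 40, mean 200 | 0.20 | 20 | 20/200 = 0.100 |
| SD 30, mean 150 | 0.20 | 20 | 20/150 = 0.133 |

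The ratio is 0.133/0.100 = 1.33, although relative variability is identical. At constant CV the index is proportional to 1/mean, so a fall in the mean from 200 to 150 gives 200/150 = 1.33 whatever the CV. A second pair behaves the same way: SD 35 at mean 140 and SD 45 at mean 180 both have CV 25%, but give 0.179 and 0.139, a 22% difference.

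**SD divided by the mean.** SD/mean = CV%/100. If CV% is not divided again, these two indices carry the same information.

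**MAGE divided by the mean.** The powered 25 mg/dl becomes 25/140 = 0.179 to 25/200 = 0.125 for assumed common means of 140 to 200. If the arms differ in mean, the contrast itself changes. Take MAGE 75 against 100 mg/dl:

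- equal means: 75/100 = 0.75, a 25% reduction;
- means 150 and 170: 0.500 against 0.588, ratio 0.85, a 15% reduction;
- means 170 and 150: 0.441 against 0.667, ratio 0.66, a 34% reduction.

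The standardised effect 25/16 = 1.56 would carry over only if all patients had the same mean glucose. Otherwise the SD of the ratio is needed, and the article does not give it, so no sample size can be computed for MAGE/mean.

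**MAGE on consecutive values.** With an assumed SD of 30 to 50 mg/dl, a 5-minute step above 1 SD needs 30/5 = 6 to 50/5 = 10 mg/dl per minute. In an assumed three-meal trace of 288 values (SD about 27, noise 0 to 4 mg/dl), the largest 5-minute step was 17 to 23 mg/dl. None of the 287 differences qualified, while peak-to-nadir MAGE was 71 to 80 mg/dl. In 2,000 simulated three-meal days, 1.15% had any qualifying step, and mean peak-to-nadir MAGE was 78 mg/dl.

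**The case against.** The strongest reply is that this is one condensed sentence in an article, with references and no printed formula. Since CV% is normalised by construction, the word all may describe the set without ordering a second division, and the blood-pressure definition shows that the authors know what a CV is. The reference to each period fits the 6-hour blocks, from which MAGE is excluded. The general sentence on using methods as in the literature points to standard computation, and expressing variability relative to the mean is a recognisable choice when means differ.

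Much of this stands as an explanation of how the sentence arose, and the analysts may well compute the indices correctly. It does not repair the text. MAGE heads the list that the rule covers, and a general assurance does not override an explicit rule or say which MAGE scale is analysed.

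Three stronger readings are tempting but not supported:

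- A reader might infer that CV% is normalised twice and also duplicated by the normalised SD. These belong to different readings: taken literally, CV%/mean and SD/mean are different numbers; with CV% divided once, they coincide. The duplication alone is redundant and biases nothing.
- A reader might infer that MAGE could not be computed. The article speaks of points, while it uses readings for the 5-minute values, and the Background speaks of peaks and nadirs. Successive turning points are probably meant, and an empty set of excursions would be obvious to any analyst.
- A reader might infer that variance should be dropped because it is SD squared. That is a preference, not an error.

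**Conclusion.** Wrong as written, moderate severity. Two parts need no simulation. Applied literally, the normalisation rule turns CV% into an index that varies inversely with mean glucose at constant CV, and under the alternative reading the normalised SD adds nothing. The same rule puts MAGE on a unitless scale, while the sample size is in mg/dl. The third part, the MAGE wording, is a matter of clarity.

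The 33% figure and the 15% to 34% spread depend on assumed means, SDs and MAGE values, and show direction and possible size only. The documents do not show that the indices will be computed wrongly, nor that mean glucose will differ between arms. They show a stated rule for the primary outcome that should not be followed as it stands, and an unsettled scale for the powered index.

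**What to change.** Replace the two sentences on normalisation and MAGE so that they state:

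- MAGE and SD are analysed in mg/dl, and variance, if kept, in its own units (mg/dl squared);
- CV% is computed once as 100·SD/mean and is the only conventional index normalised by the mean;
- MAGE is the mean of the absolute differences between successive glucose peaks and nadirs that exceed 1 SD of that 24-hour series;
- MAGE/mean, if wanted, is reported only as a sensitivity index.

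This puts the analysed MAGE on the scale of the sample size calculation. It costs two sentences and needs no new data or measurements. The Trial status section describes recruitment as not yet begun, so on the article's own account the change can be made before any data exist.

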### Metabolic evaluation

Peripheral venous blood will be collected into 10 ml vacutainer tubes, and used to perform the blood tests; these samples will be stored at −20°C. Glucose, HbA1c, insulin, glucagon, and glucagon-like peptide 1 (GLP-1) will be assayed.

### Oxidative stress evaluation

The 24-hour urinary samples will be collected at visits 1 and 6 and used to evaluate creatinine and 8-isoprostaglandin F2α (8-isoPGF2α), which is considered a well-recognized marker of oxidative stress [19]. This isomer will be measured using a competitive enzyme-linked immunoassay (ELISA) (Cell Biolabs Inc. San Diego, CA USA).

### Cardiovascular evaluation

Cardiac output and heart rate will be measured before (10 minutes at rest) and during the submaximal exercise test and after 60 minutes of recovery, using a non-invasive method. The data will be recorded (MP150 system; Biopac Santa Barbara, CA, USA) using a general purpose amplifier module (DA100; Biopac), impedance cardiography (NICO100C; Biopac) and electrocardiogram (ECG100C; Biopac), according to methodological guidelines provided by Sherwood *et al*. [20].

To assess the cardiovascular autonomic control, heart rate variability (HRV) analysis will be applied. Pulse intervals (PI) series (tachograms) will be obtained from the electrocardiography records. Stationary segments (300 beats), coincident in the tachogram, will be selected, and spectral analysis will be performed using an autoregressive model, which estimates the center frequency and power of each relevant oscillatory component. The spectral bands for humans are defined as very low frequency (VLF), for 0.0 to 0.04 Hz, low frequency (LF), for 0.04 to 0.15 Hz, and high frequency (HF) for 0.15 to 0.40 Hz intervals, defined according to previous references [17]. Tachogram spectra will be evaluated quantitatively, and values of HRV will be obtained, as well as its spectral components, and will be expressed in absolute (ms2). In additional, LF and HF bands will be expressed in normalized units (NU), obtained by calculating the power of LF and HF spectra, and correlating them with the total power without the VLF component [17].

Of the parameters that can be obtained by spectral analysis, those distinguished for their physiological significance are the LF and HF components, which are mainly related to sympathetic and parasympathetic cardiac modulations, respectively. The relationship between them – the LF/HF index, or sympathetic-vagal balance [21] – will be evaluated.

Patients will be submitted to a 24 hour ABPM on a usual work day, using a monitor (model 90207; Spacelabs, Redmond, WA, USA) that will be programmed to automatically measure BP every 15 minutes during the day (06.00 to 22.00 hours), and every 20 minutes during the night (22.00 to 6.00 hours) [22, 23]. BP variability will be assessed from BP behavior in different windows of a 24 hour period, covering both daytime and night-time periods. The cuff size will be adapted to the circumference of the arm of each patient according to the manufacturer’s recommendations.

Based on the results of the 24 hour ABPM, the mean 24 hour systolic BP (SBP) and diastolic BP (DBP) will be calculated for each patient, before and after treatment. Three different parameters of SBP variability will be calculated: 1) time–rate index (rate of change in SBP over time in mm Hg/min, defined as the first derivative values of SBP by time); 2) coefficient of variation of the 24 hour SBP (SD/mean pressure × 100%); and 3) mean of the SD of the 24 hour SBP. The time–rate index allows the calculation of the sum of angular coefficients, and aims to measure how fast or how slow SBP values are and in which direction they change. The measure will be calculated using the formula,

where *r* is the rate of BP variability over time (considering the differences between BP measurements at each time interval) and *N* is the number of recordings [24]:

### Endothelial function evaluation

This analysis will be performed by a high-resolution ultrasound of the brachial artery (vascular Doppler), which characterizes the flow-mediated dilatation (FMD). FMD is expressed by changes in basal diameter in response to the increased flow and to nitroglycerin, which will be administered in a single dose (0.4 mg, sublingual spray). The equipment used will be an HD7XE (Philips, Bothell, WA, USA) with an HF transducer (3 to 12 MHz; L12-3; Philips) [25].

### Ethics and data protection issues

Participation will be voluntary, and will follow the ethical aspects of confidentiality and data protection. Procedures will be explained to patients, and information about the aim, design, associated potential risks and benefits and all relevant details of the research will be given in the informed consent form. All patients will have to sign the informed consent form prior to participating in the study. The data obtained by the study will be available to the participant and to any other authorized person, and may be used anonymously for academic scientific purposes.

The study was approved by Scientific Committee and Research Ethical Comission (IRB number 120444) of Hospital de Clínicas de Porto Alegre (Brazil), which is part of National Committee of Ethics in Research. Approval Number: 10662912.3.0000.5327.

### Safety assessment

Adverse events (AEs), including serious adverse events (SAEs) or pregnancies will be collected and included in the medical reports. The reports containing details of SAEs or pregnancies will be forwarded to the laboratory of the respective manufacturer within 24 hours, and to the health authorities.

To ensure patient safety, the individuals participating in the research will be monitored for the occurrence of all AEs after beginning the specific protocol procedures until 4 weeks after the patient discontinues participation in the study.

### Statistical analysis plan

Data will be analyzed using SPSS software (Statistical Package for Social Sciences; version 18.0 for Windows, SPSS Inc., Chicago, USA). The description of values will be expressed as mean ± SD. The statistical procedures used will be Student’s *t*-test for independent samples (intergroup analysis), paired *t*-test (intragroup analysis), and analysis of variance (ANOVA) for repeated measures to compare both groups at different times. A Pearson correlation will be performed between measures of glucose variability and 8-isoPGF2α/crn. The statistical power will be 90%, and the accepted level of significance will be *P* < 0.01.

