**Methods/Design:**

This study is a PROBE (Prospective, Randomized, Open-label, Blinded-Endpoint) design clinical trial.

The estimated sample needed is 20 patients with T2DM. In addition to the routine treatment (metformin), patients will receive a second drug orally for 12 weeks: the METV group will receive metformin plus vildagliptin (50 mg twice daily), and the METG group will receive metformin plus glibenclamide (5 to 10 mg twice daily.). Before and after intervention, evaluation of glycemic variability, endothelial function, oxidative stress, and metabolic and cardiovascular response will be performed at rest, during and after a submaximal exercise test (30 minutes, with an intensity based at 10% under the heart rate at the second threshold).

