### Data collection

Eligible patients will initially perform a maximum effort test, and 48 hours later, they will begin the study protocol, as follows:

Day 1: Begin 24-hour urinary collection, perform vascular Doppler ultrasound to evaluate endothelial function, and then insert glucose sensor subcutaneously to begin continuous glucose monitoring system (CGMS) evaluation.Day 2: End the 24-hour urinary collection, carry out the submaximal exercise test (with blood collection at baseline, 15, and 30 minutes into the session, and 60 minutes after recovery). Assess heart rate variability 10 minutes before and after the submaximal exercise test, and begin 24 h ambulatory blood pressure monitoring (ABPM).Day 3: Removal of the glucose sensor; end 24 h ABPM. Randomization.

This same protocol will be repeated at the end of the 12-week treatment with vildagliptin or glibenclamide.

The experimental sessions will occur at the Exercise Pathophysiology Research Laboratory, Hospital de Clínicas de Porto Alegre (LaFiEx-HCPA), maintaining the ambient temperature at between 20 and 22°C.Patients will be asked to follow their habitual diet during the 3 days of protocol. To carry out the submaximal exercise test they will go to LaFiEx-HCPA in a fasted state. Patients will record detailed food intake in diaries across the 3 days of CGMS use. The dietary assessment will be performed using the software DietWin (DietWin, Porto Alegre, Brazil). In addition, participants will be instructed to avoid intense activities and not to consume caffeinated beverages on the day before the dietary assessment, in order to exclude any residual effect before and after the effort test. The submaximal exercise test will occur after a standard breakfast (500 kcal; 60% carbohydrate, 30% fat and 10% protein). During the drug treatment period (12 weeks) patients will not follow any kind of physical exercise program. The flow diagram of the study design is shown in Figure 1.

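### Neither stated between-arm analysis is baseline-adjusted, although every outcome is measured before randomization; ANCOVA on week-12 MAGE would gain about 1 to 26 points of power over the t-test if the unstated correlation is 0.3 to 0.7

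*Protocol article*

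**What the plan says.** The Statistical analysis plan section of the protocol article names three procedures for comparing means:

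- an independent-samples t-test between arms ("test for independent samples (intergroup analysis");
- a paired t-test within arms ("test (intragroup analysis");
- "analysis of variance (ANOVA) for repeated measures to compare both groups at different times".

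No model with baseline as a covariate is named, and none of the three is designated the primary test. The section does not say whether the independent-samples test is applied to week-12 values or to change. The Sample size calculation section points to week-12 values, because it sizes the trial with a two-sided unpaired t-test on "MAGE levels (mean ± SD) of 25.0 ± 16 mg/dl at week 12".

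The baseline data will exist. The abstract states: "Before and after intervention, evaluation of glycemic variability, endothelial function, oxidative stress". Under Data collection, the urine collection, vascular ultrasound, glucose monitoring, exercise test and ambulatory blood pressure come on days 1 to 3, with randomization listed last on day 3. Then: "This same protocol will be repeated at the end of the 12-week treatment with vildagliptin or glibenclamide".

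**The concern.** A measurement of the outcome taken before randomization is a legitimate covariate and often a strong one. The two stated between-arm analyses sit at opposite extremes. A t-test on week-12 values gives baseline no weight. A change score, which is what the group-by-time test amounts to on two occasions, subtracts all of it. ANCOVA estimates the weight from the data.

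This matters more in a very small trial. With 9 per arm and an assumed baseline SD of 16 mg/dl, the standard error of the chance baseline difference is 16 × sqrt(2/9) = 7.5 mg/dl, or 7.5/25 = 30% of the target effect. The week-12 t-test leaves the effect of such an imbalance in the estimate, and the change score over-corrects for it whenever the regression slope is below 1.

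The paired tests do not help here. The stated hypothesis is a greater improvement on vildagliptin than on glibenclamide, and a within-arm test cannot address that.

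**Working it through.** **Inputs from the Sample size calculation section.** Difference 25 mg/dl, SD 16 mg/dl, two-sided alpha 0.01, power 90%, total 20 including 10% dropout. That leaves 20 × 0.9 = 18 evaluable, or 9 per arm. Equal arms are assumed, because no allocation ratio is stated.

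**Input not in the article.** The correlation rho between baseline and week-12 MAGE. It is varied from 0 to 0.8, with equal SDs at both times.

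**Step 1: the plan's own figure.** By the normal approximation, n per arm = 2 × (2.576 + 1.282)² × (16/25)² = 2 × 14.88 × 0.4096 = 12.2, so 13 per arm, 26 in total, and 26/0.9 = 28.9, so 29 with dropout. With the t distribution it is 14 per arm, 28 in total, and 32 with dropout. The stated 20 is not reproduced. That is a separate matter, but it sets the starting point here.

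**Step 2: the stated t-test.** Noncentrality = 25 / (16 × sqrt(2/9)) = 25/7.54 = 3.31 on 16 degrees of freedom, which gives 65% power.

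**Step 3: the alternatives.**

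- Change score: SD = 16 × sqrt(2(1 − rho)), 16 degrees of freedom.
- ANCOVA: residual SD = 16 × sqrt(1 − rho²), 15 degrees of freedom, plus the extra variance from the chance baseline difference. Residual variance falls by rho²: 9%, 25% and 49% at rho 0.3, 0.5 and 0.7.

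The small-sample penalties matter at this size, so power was simulated with 100,000 trials per setting (bivariate normal; Monte Carlo standard error about 0.15 points).

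| rho | Week-12 t-test | Change score | ANCOVA | ANCOVA minus t-test |
|---|---|---|---|---|
| 0 | 65% | 32% | 61% | −4 |
| 0.2 | 65% | 41% | 63% | −2 |
| 0.3 | 65% | 47% | 66% | +1 |
| 0.4 | 65% | 55% | 70% | +5 |
| 0.5 | 65% | 65% | 76% | +11 |
| 0.6 | 65% | 77% | 83% | +18 |
| 0.7 | 65% | 90% | 92% | +26 |
| 0.8 | 65% | 98% | 98% | +33 |

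The last column is in percentage points, taken before rounding.

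**Step 4: no dropout.** With 10 per arm the t-test has 72% power, and ANCOVA 74%, 83% and 95% at rho 0.3, 0.5 and 0.7.

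**Reading the table.** ANCOVA is at least level with the change score at every rho shown. It breaks even with the week-12 t-test just below rho 0.3 and gains 10 points or more from about 0.5. The two stated tests can differ by 25 points in favour of the change score (rho 0.7) or by 18 points in favour of the t-test (rho 0.3), so choosing between them would mean guessing rho.

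**The case against.** The strongest reply is that the gain rests on a number the article does not give. MAGE is computed over 24 hours, and 12 weeks of treatment separate the two recordings, so a correlation of 0.5 or more cannot be taken for granted. This stands. A reader might infer that adjustment brings clearly more power for nothing; the table does not support that. The gain is negligible at 0.3 and turns into a small loss below it.

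A reader might also infer that the plan ignores baseline, or that its between-arm test is invalid. Neither follows. Repeated-measures ANOVA uses the baseline value, though with a fixed weight, and chance imbalance does not bias a t-test under randomization.

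On the paired tests, the article labels them only as within-group and nowhere says they will be offered as evidence of a drug difference. Patients are selected on HbA1c, not MAGE, so regression to the mean in the primary index would be indirect and of unknown size. What remains is that these tests cannot answer the comparative question.

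Nor does the article support a claim that repeated-measures ANOVA would lose many patients to incomplete series. It gives no rate of missing samples, and samples drawn in one supervised session would tend to be lost together.

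Finally, covariates are often left to a fuller analysis plan. Here, however, the article has a section of that name and lists the tests, so the point concerns what is stated rather than a detail left out.

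**Conclusion.** The point holds as a recommendation on efficiency. Against the week-12 t-test, ANCOVA is worth about +1, +11 and +26 points of power at rho 0.3, 0.5 and 0.7, and −2 to −4 points at rho 0.2 to 0. Against the change score it gains 19, 11 and 2 points at 0.3, 0.5 and 0.7. These figures assume normal data, equal SDs at both times, 9 per arm, and the article's difference, SD and alpha.

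If the independent-samples test was meant for change rather than week-12 values, the change-score column applies and the conclusion is the same.

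ANCOVA does not repair the sample size. The stated 90% power is reached with 9 per arm only if rho is near 0.7. The gap between 65% and 90% comes mainly from a total of 20 that does not follow from the stated alpha and power.

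**What to change.** Name one primary between-arm analysis: ANCOVA of week-12 MAGE with arm and baseline MAGE as terms, reported as the adjusted mean difference with its confidence interval. Label the paired t-tests as descriptive, and say which outcomes the repeated-measures ANOVA serves. State the correlation assumed and give power over a range of it, including values at which ANCOVA gains nothing.

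The cost is a change of wording, one degree of freedom (16 to 15 with 18 evaluable patients), and the small loss shown above if rho is 0.2 or lower. No new data are needed. The choice should be fixed before any outcome data are examined; the article describes the trial as not yet recruiting.
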